## **D.8. Data Analysis**

### **D.8.1. Data Management, Exploratory Data Analysis, Missing Data, and Psychometrics**

Data will be organized and cleaned following quality control procedures developed in the SAAF trial, which involve checking for outlying values and inappropriate patterns of missing data. Next, items' distributions and constructs' psychometric properties will be examined. Both exploratory and confirmatory factor analyses will be conducted, using data transformations and factor analysis with ordinal scales where the data's distributions warrant it (Muthén & Muthén, 2004). Mplus (Muthén & Muthén, 2004), a comprehensive structural equation and growth curve modeling program, will be used to examine the stability of the scales' factor structure across the pretest, posttest, and long-term follow-up assessments. Mplus permits construction of sophisticated structural equation models and handles missing data using full maximum likelihood methods in which all available data are included under a "missing at random" assumption. These solutions will be compared to models that allow certain types of non-ignorably missing data to assess the stability of these assumptions (Brown, Indurkha & Kellam, 2000). Standard exploratory data analytic methods will be used to examine departures from normality and to determine the type of modeling that is required. For example, substance use and sexual behavior variables typically include large proportions of abstainers along with a skewed distribution of engagement in high-risk behavior. These types of data, which routinely have been analyzed by creation of abstinent/nonabstinent dichotomies or treated as continuous normal-like variables, will be examined using more complex two-part models (Olsen & Schafer, 2001) that allow separate tracking of the intervention's impact on abstinence/ nonabstinence and levels of risk behavior. Finally, for many of the analyses of intervention-targeted behaviors and attitudes, confirmatory factor analyses will be used when possible to form latent constructs by combining data from different informants. If the informants' perspectives do not converge enough to make this possible, each informant's data will be included in the analyses as a separate variable.

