### Trials Protocols

#### SAAF-T

##### A. SPECIFIC AIMS

In this proposal, we request funding to conduct a randomized prevention trial to test the SAAF–HS program’s efficacy. The sample will include ~500 rural African American families with a 10th-grade student, half of whom will be assigned randomly to a SAAF–HS and half to an attention-control group. Pre-intervention, post-intervention, and long-term follow-up assessments of adolescents’ substance use and high-risk sexual behavior will be gathered from the entire sample.

Our specific aims are as follows:

1. To test the hypothesis that rural African American adolescents randomly assigned to participate in SAAF–HS, compared to attention-control participants, will demonstrate lower rates of substance use initiation, and that those who already use substances (e.g., cigarettes; alcohol, including binge drinking; marijuana and other illicit substances) will use them less frequently and consume lower quantities at each follow-up assessment.
2. To test the hypothesis that rural African American adolescents randomly assigned to participate in SAAF–HS, compared to attention-control participants, will demonstrate lower rates of high-risk sexual behavior (e.g., instances of unprotected sexual intercourse, multiple sexual partners) at each follow-up assessment.

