#### **D.7.7. Adolescents' Outcomes**

**D.7.7a. Substance use.** The substance use assessment is designed to address its multidimensional nature (Newcomb, 1992). From three well-validated measures, items were selected for their sensitivity to intervention effects at several levels of substance use. At the initiation level, group differences in the proportion of participants who transition from nonuse to use during the study can be detected. At the escalation level, group differences in the proportion of participants who increase their frequency/intensity of use during the study can be assessed. At the problem use level, group differences in specific substance-related behaviors and problems can be determined. The basic items in the measure are those included in the Monitoring the Future study (Johnston et al., 2004) that assess lifetime, annual, and 30-day prevalence and frequency of cigarette smoking, alcohol use, binge drinking, and marijuana use. For the purposes of the proposed study, a 6-month assessment at the long-term follow-up will be added. A checklist of other drugs includes lifetime use of LSD/acid, MDMA/Ecstasy, cocaine, heroin, other opiates, amphetamines, non-prescribed tranquilizers, and inhalants. Problems associated with substance use will be indexed using items from the Minnesota Student Survey for high school students (Harrison, Fulkerson, & Beebe, 1998) These scales include items assessing dependence (e.g., had to use more to get same effect, tried to cut down but couldn't) and negative consequences of use (e.g., use hurt relationships with friends or family, use interfered with other activities, use resulted in problems with law, missed school or work because of use).

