### **D.8.2. Analyses for Aims 1 and 2: Primary Outcomes**

The primary issue to be addressed in Aims 1 and 2 is SAAF-HS's effectiveness in deterring the onset and escalation of substance use and high-risk sexual behavior across the 18 months separating the pretest and long-term follow-up assessments. A dramatic growth in substance use and high-risk sexual behavior is likely to occur across measurement points, which include the beginning of 10th grade, middle of 10th grade, and beginning of 11th grade. SAAF-HS's impact on each of the outcomes will be examined in three ways: on posttest (middle of 10th grade), on long-term follow-up (beginning of 11th grade), and on growth trajectories. The two single-time-point analyses will be conducted with Structural Equation Modeling (SEM) using the maximum likelihood method and controlling for baseline levels of substance use and high risk-sexual behavior. The first outcome analysis (posttest) identifies reduction in substance use and high risk-sexual behavior; the second (long-term follow-up) will be used for tests of delayed initiation and reduction of substance use and reduction of high-risk sexual behavior. We will explore, in an additional analysis, SAAF-HS's effects on delaying the onset of sexual intercourse. SAAF-HS, however, is likely to have its strongest impact on growth trajectories (Taylor et al., 2000). A baseline growth model with random intercepts and slopes will be established for the attention-control condition. A multigroup analysis will then be conducted, testing the equivalence of growth parameters between the attention-control and the SAAF-HS groups (Byrne, 2001). If the multigroup analyses detect differences between the slopes (rates of growth for substance use or high-risk sexual behavior) of the SAAF-HS and attention-control group, impact statements will be made by examining how the average substance use and sexual risk behavior trajectories change with time.

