### **D.8.6. Statistical Power**

In this section, we discuss statistical power for the models we described previously, including the SAAF–HS intervention’s impact on changes in the slopes of drug use and high-risk sexual behavior and on outcomes at a single point in time. In these calculations, we assume conservatively a 13% loss in data across time, yielding two groups of 250 participants in each condition. For growth models with either continuous or discrete outcomes, we have used power calculations that Brown and colleagues have made available on the internet (<http://psmq.usf.edu/products.html>) to determine the smallest effect size we can detect with 80% power for changes in the slope parameter, assuming linear growth over three time points. When the measurement reliability is 60%, we can achieve 80% power when the ES is 0.1 at posttest and grows to 0.2 at long-term follow-up. For conducting a test at a single time point on a continuous outcome, based on Cohen (1988), we can detect an effect size of 0.25 at 80% for a 0.05 level test, assuming negligible variation based on school. We also have calculated power by taking this factor into account. Based on variability observed in other preventive trials among schools and individuals (Brown and Liao, 1999) the power is 80% to detect an ES of 0.36 and 70% to detect an ES of 0.31 for 0.05 level tests. Thus, we clearly have adequate power to detect a moderate effect for continuous outcomes involving single time points. For a discrete measure at a single time point, such as a comparison of the proportion of individuals who are using a substance, we will be able to detect an odds ratio of at least 1.6 with 80% power using a 0.05 level chi-square test (Fleiss et al., 2003). This odds ratio corresponds to a reduction from 50% users to 38% in the intervention group.

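### SAAF-T: the level part of the planned two-part model compares adolescents using at each assessment, which is neither a randomised comparison nor the group named in Aim 1's second hypothesis

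*Combined protocol and SAP*

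**What the plan says.** All references are to the SAAF-T protocol.

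- **Aim 1 (Section A)** has two hypotheses. Adolescents assigned to the programme "will demonstrate lower rates of substance use initiation". Separately, "those who already use substances (e.g., cigarettes; alcohol, including binge drinking; marijuana and other illicit substances) will use them less frequently" and in lower quantities. The second concerns a group whose status can be fixed at pretest.
- **D.8.1** says that substance use and sexual behaviour variables with many abstainers "will be examined using more complex two-part models", which "allow separate tracking of the intervention's impact on abstinence/ nonabstinence and levels of risk behavior". It does not define the level part, say how the two parts are linked, or say how the level coefficient will be read.
- **D.8.2** names the analyses for Aims 1 and 2. These are structural equation models at posttest and at long-term follow-up, "controlling for baseline levels of substance use and high risk-sexual behavior", and multigroup growth models. None is described as restricted to users at follow-up, and none is specified for pretest users.
- **D.7.7a** describes escalation over all participants: "group differences in the proportion of participants who increase their frequency/intensity of use during the study can be assessed".
- **D.8.6** gives the only use rates in the SAAF-T plan: "This odds ratio corresponds to a reduction from 50% users to 38% in the intervention group".

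**The concern.** A two-part model has one part for any use and one for amount given use. The second part draws its information from non-zero observations, so its programme coefficient describes adolescents who are using at that assessment. Use at follow-up is itself an outcome of randomisation. If the programme works as the first hypothesis predicts, the users left in the programme arm are a selected subset of those who would have used without it, and the two groups of users need not be alike.

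The analysed group is also not the one Aim 1 names. Current users at follow-up include new initiators and exclude pretest users who have stopped. The second hypothesis is about "those who already use substances". A reader looking for its test could easily take the level coefficient as the answer. Where prevention falls mainly on lighter users, that coefficient would understate a benefit on amount used, or reverse its sign, even though total use in the arm had fallen.

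**Working it through.** **Inputs from D.8.6.** 50% users in control and 38% under the programme; 250 per arm, taken as stated; 0.05 level; 80% power; detectable effect 0.25 SD for a continuous outcome at one time point. **Assumed, because the documents give no figure:** pretest use of 10% to 30%; log level among would-be users normal with SD 1; how prevention depends on level.

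**1. The plan's own figures.** With z = 1.96 + 0.84 = 2.80, the detectable difference at 250 per arm is 2.80 × √(2/250) = 0.25 SD, which reproduces the plan. The odds ratio for 50% against 38% is 1/(0.38/0.62) = 1.63. Two-sided power for that contrast at 250 per arm is 77.3%, slightly under the stated 80%. The rates serve below only as an illustration.

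**2. Who remains in the comparison.** Users at follow-up: 0.50 × 250 = 125 in control and 0.38 × 250 = 95 under the programme. Share of would-be users prevented: 0.12/0.50 = 24%.

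**3. Shift in a simple comparison of current users, with no effect on anyone's level.**

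| Who is prevented | Formula | Shift (SD) |
|---|---|---|
| A random 24% | – | 0 |
| Lightest 12%, and 12% at random | φ(−1.175)/0.88 = 0.200/0.88 | 0.23 |
| Lightest 24% | φ(−0.706)/0.76 = 0.311/0.76 | 0.41 |

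Letting the chance of prevention fall gradually with level (logit slopes 0.5, 1 and 2) gives 0.12, 0.20 and 0.31 SD. Across the range from random prevention to the lightest 24%, the ratio of whole-sample mean use, programme to control, is 0.76 to 0.96. It falls in every case, while the current-user mean is unchanged or rises.

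**4. Detectable difference among current users.** 2.80 × √(1/125 + 1/95) = 2.80 × 0.136 = 0.38 SD. This is the benchmark for the shifts in step 3. The plan's 0.25 SD assumes all 250 per arm.

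**5. Only new initiation prevented.** In 2,000 simulated trials per setting, with pretest use of 10% to 30% and slopes of 1 to 2, the current-user difference averaged 0.10 to 0.28 SD. Adjusting for pretest use (yes/no) left 0.13 to 0.29 SD. Among pretest users the difference was about 0; that follows from the set-up, since nobody in that group was affected.

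**6. Precision of a pretest-user comparison.** At 10% pretest use there are 25 per arm: 2.80 × √(2/25) = 0.79 SD. At 30% there are 75 per arm: 2.80 × √(2/75) = 0.46 SD.

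**The case against.** The strongest reply is that the two-part model is not the named primary analysis. It appears as an example in the section on data management and exploratory work. D.8.2, which is headed as the analysis of the primary outcomes, lists models not described as conditioning on follow-up use, and its impact statements rest on average trajectories. This stands, and it rules out the inference that Aim 1 depends on current users alone. What remains is that D.8.1 commits to these models for this kind of outcome without relating them to D.8.2, and no section specifies a pretest-user analysis.

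A second reply is that the calculation is a raw single-visit contrast. The methods paper cited in D.8.1 is, by its title in the reference list, about a two-part model with random effects for longitudinal data, and the trial has three waves. If the parts are linked through correlated random effects, the shift may be smaller. This also stands: the figures are not the bias of that model, which was not evaluated. The plan does not state the linkage, and the coefficient would still concern level given use.

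A reader might infer that the programme will look harmful. The documents do not support that. It requires prevention to be concentrated in lighter users, on which they are silent; the shift is zero if prevention is unrelated to level; and 50% to 38% is a detectable difference, not a forecast. A reader might also set the shift against the plan's 0.25 SD. That benchmark does not apply to about 125 against 95 users. Against 0.38 SD, only the extreme case is larger.

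**Conclusion.** The concern holds as a mismatch between hypothesis and analysis. The level comparison among current users is not a randomised one, and it does not address the group in Aim 1's second hypothesis. That conclusion follows from the aims and from how a two-part model is built; it needs no assumption about who is prevented.

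The numerical size is conditional. At the plan's illustrative rates, a simple comparison shifts by 0 to about 0.4 SD with no effect on any individual's level. This rests on a normal log level, no true effect on level, and an assumed link between level and prevention. The any-use part still addresses the first hypothesis validly. The point should be settled before analysis, but it does not undermine the D.8.2 models as described.

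**What to change.** State in D.8.1 and D.8.2 how the two-part models relate to the structural equation and growth models, and add three items:

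1. For all randomised adolescents, report the overall mean difference in use that combines both parts (probability of use times mean level given use), as the main estimate of effect on amount used.
2. Compare frequency and quantity between arms among adolescents reporting use at pretest, counting those who stop as zero, as the direct test of Aim 1's second hypothesis.
3. Label the level coefficient among current users as descriptive, and say how the two parts are linked.

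The cost is analysis-plan wording, one derived estimate from the same model and one additional comparison. Pretest use is already collected. The downside is precision: the pretest-user comparison could detect only about 0.46 to 0.79 SD if 30% to 10% use at pretest, an assumed range. It should therefore be reported beside the whole-sample estimate and not in place of it.

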### **D.8.2. Analyses for Aims 1 and 2: Primary Outcomes**

The primary issue to be addressed in Aims 1 and 2 is SAAF-HS's effectiveness in deterring the onset and escalation of substance use and high-risk sexual behavior across the 18 months separating the pretest and long-term follow-up assessments. A dramatic growth in substance use and high-risk sexual behavior is likely to occur across measurement points, which include the beginning of 10th grade, middle of 10th grade, and beginning of 11th grade. SAAF-HS's impact on each of the outcomes will be examined in three ways: on posttest (middle of 10th grade), on long-term follow-up (beginning of 11th grade), and on growth trajectories. The two single-time-point analyses will be conducted with Structural Equation Modeling (SEM) using the maximum likelihood method and controlling for baseline levels of substance use and high risk-sexual behavior. The first outcome analysis (posttest) identifies reduction in substance use and high risk-sexual behavior; the second (long-term follow-up) will be used for tests of delayed initiation and reduction of substance use and reduction of high-risk sexual behavior. We will explore, in an additional analysis, SAAF-HS's effects on delaying the onset of sexual intercourse. SAAF-HS, however, is likely to have its strongest impact on growth trajectories (Taylor et al., 2000). A baseline growth model with random intercepts and slopes will be established for the attention-control condition. A multigroup analysis will then be conducted, testing the equivalence of growth parameters between the attention-control and the SAAF-HS groups (Byrne, 2001). If the multigroup analyses detect differences between the slopes (rates of growth for substance use or high-risk sexual behavior) of the SAAF-HS and attention-control group, impact statements will be made by examining how the average substance use and sexual risk behavior trajectories change with time.

The three-time-point design allows one degree of freedom in fitting linear growth patterns. An exploratory analysis will be conducted to assess nonlinearity in growth over time (Wang, Brown & Bandeen-Roche, 2005). If these diagnostic patterns indicate nonlinearity, the fit will be improved through transformation of the time axis by freeing the last loading, effectively incorporating nonlinearity. Separate analyses will be used to examine impact on alcohol, tobacco, and marijuana use because different intervention impacts occasionally emerge for different substances. In all these models, fit will be compared using formal likelihood ratio statistics, Wald-type tests, and diagnostic techniques that Brown and colleagues developed (Wang, Brown & Bandeen-Roche,

2005). For analyses of high-risk sexual behavior, two outcomes, unprotected sex at last encounter and number of unprotected encounters in the past 3 months, will be analyzed using binary outcomes and Poisson counts, respectively. For each of these repeated measures, we anticipate two types of “zeros”: one indicating abstinence and another indicating condom use. Two approaches will be used, one that incorporates a separate model of abstinence and condom use over time as a function of intervention condition and another that models these outcomes as “zero-inflated” Binomial and Poisson models, similar to Carlin et al.’s (2002) modeling of smoking behavior.

### **D.8.3. Analysis of Aims 3 and 4: Changes in Intervention-targeted Behaviors**

Aims 3 and 4 focus on SAAF–HS’s impact on competence-promoting and responsive family relationships and protective adolescent mediators. These aims will be analyzed using the same methods used for aims 1 and 2. SAAF–HS’s impact on the outcome variables will be analyzed with posttest, long-term follow-up, and growth trajectory data. The two single-time-point analyses will be conducted using SEM, controlling for baseline levels of the outcome variables. Again, SAAF–HS should evince its strongest impact on growth trajectories. The same method used to analyze growth trajectories for Aims 1 and 2 will be used for Aims 3 and 4.

### **D.8.6. Statistical Power**

In this section, we discuss statistical power for the models we described previously, including the SAAF–HS intervention’s impact on changes in the slopes of drug use and high-risk sexual behavior and on outcomes at a single point in time. In these calculations, we assume conservatively a 13% loss in data across time, yielding two groups of 250 participants in each condition. For growth models with either continuous or discrete outcomes, we have used power calculations that Brown and colleagues have made available on the internet (<http://psmq.usf.edu/products.html>) to determine the smallest effect size we can detect with 80% power for changes in the slope parameter, assuming linear growth over three time points. When the measurement reliability is 60%, we can achieve 80% power when the ES is 0.1 at posttest and grows to 0.2 at long-term follow-up. For conducting a test at a single time point on a continuous outcome, based on Cohen (1988), we can detect an effect size of 0.25 at 80% for a 0.05 level test, assuming negligible variation based on school. We also have calculated power by taking this factor into account. Based on variability observed in other preventive trials among schools and individuals (Brown and Liao, 1999) the power is 80% to detect an ES of 0.36 and 70% to detect an ES of 0.31 for 0.05 level tests. Thus, we clearly have adequate power to detect a moderate effect for continuous outcomes involving single time points. For a discrete measure at a single time point, such as a comparison of the proportion of individuals who are using a substance, we will be able to detect an odds ratio of at least 1.6 with 80% power using a 0.05 level chi-square test (Fleiss et al., 2003). This odds ratio corresponds to a reduction from 50% users to 38% in the intervention group.

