##### D. RESEARCH METHODS

###### D.1. Participants

A random sample of 500 rural African American families with a son or daughter in the first semester of 10th grade in a public high school will participate in the study.

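### SAAF-T's power figures count all 250 youths per arm, but its condom-use comparisons draw only on sexually active youths, so the stated power does not apply to those comparisons

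*Combined protocol and SAP*

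**What the plan says.** All references are to the SAAF-T part of the combined document.

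- **Scope of the power section.** D.8.6 says it covers the models set out earlier in the plan, including the intervention's "impact on changes in the slopes of drug use and high-risk sexual behavior and on outcomes at a single point in time".
- **Numbers used.** D.8.6 states "we assume conservatively a 13% loss in data across time", "yielding two groups of 250 participants in each condition". The 13% loss is the only reduction it mentions.
- **Stated effects.** For a continuous outcome at one time point, "we can detect an effect size of 0.25 at 80% for a 0.05 level test", with school variation neglected. Allowing for schools, the effects are 0.36 at 80% power and 0.31 at 70%. For a discrete outcome the figure is an odds ratio of 1.6, illustrated as 50% against 38% substance users. For growth models it is an effect of 0.1 at posttest rising to 0.2 at follow-up.
- **Primary sexual-risk outcome.** D.7.7b defines it as protected encounters divided by total encounters over the 30 days before the interview.
- **Analysis of sexual behaviour.** D.8.2 names two outcomes: unprotected sex at last encounter (binary) and the number of unprotected encounters in 3 months (count). It expects zeros of two kinds, from abstinence and from condom use, and plans two approaches. The first is "one that incorporates a separate model of abstinence and condom use over time as a function of intervention condition"; the second is a zero-inflated model.
- **Abstainers.** D.8.1 remarks that "substance use and sexual behavior variables typically include large proportions of abstainers". No section gives a rate.

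**The concern.** A ratio with total encounters in the denominator does not exist for a youth who had none. A model of condom use kept separate from abstinence learns about condoms only from youths who have sex. The number that matters for these comparisons is therefore the number of sexually active youths, which is smaller than 250 per arm by an amount the plan never states.

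What is at stake is how a null condom-use result would be read. D.8.6 invites the reader to treat it as coming from a test with 80% power for an effect of 0.25 or an odds ratio of 1.6. If many youths are not sexually active, the test would miss such effects much more often than one time in five. The affected measure includes the one D.7.7b declares primary for sexual risk.

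**Working it through.** **Inputs from the plan (D.8.6).** 250 per arm; 0.05 level; 80% power; effect size 0.25; odds ratio 1.6; 50% against 38%. Sidedness is not stated, so two-sided tests are assumed.

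**Assumed input.** The sexually active share *s* is not in the documents. A range of 30–60% is used, with 90% as a favourable check. The 50% control rate is the plan's own, but it was given there for substance use.

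**Step 1: reproduce the plan's figures.**

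Detectable difference in SD units = (1.960 + 0.842) × √(2/n) = 2.8016 × √(2/n).

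At n = 250: 2.8016 × 0.08944 = 0.2506. Power for 0.25 = Φ(0.25/0.08944 − 1.960) = Φ(0.835) = 79.8%. The stated 0.25 is reproduced, and it takes the full 250 per arm.

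For two proportions, p2 solves n = [1.960 √(2p̄(1−p̄)) + 0.842 √(p1(1−p1) + p2(1−p2))]² / (p1−p2)², where p̄ is the mean of p1 and p2. With p1 = 50% and n = 250, p2 = 37.6% and the odds ratio is 1.66. The plan's 50% against 38% is an odds ratio of (0.50/0.50)/(0.38/0.62) = 1.63, with 77.3% power. The discrete figure is thus reproduced only roughly.

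**Step 2: replace 250 by 250 × *s*.**

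| Active share | n per arm | Detectable ES | Power for 0.25 | Detectable OR (from 50%) | Power for 50% v 38% |
|---|---|---|---|---|---|
| 30% | 75 | 0.46 | 33% | 2.59 | 32% |
| 40% | 100 | 0.40 | 42% | 2.26 | 40% |
| 50% | 125 | 0.35 | 51% | 2.06 | 48% |
| 60% | 150 | 0.32 | 58% | 1.93 | 55% |
| 90% | 225 | 0.26 | 76% | 1.71 | 73% |

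Example, 30%: √(2/75) = 0.1633; 2.8016 × 0.1633 = 0.457; power = Φ(0.25/0.1633 − 1.960) = Φ(−0.429) = 33%.

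**Step 3: the other stated figures.** The slope calculation came from an external program and the school-adjusted one from unstated variances, so neither can be rebuilt. Scaling by 1/√*s* gives an order of size only. At 30–60% active, the follow-up slope effect of 0.2 becomes about 0.37–0.26 and the school-adjusted 0.36 becomes about 0.66–0.46. The clustering penalty would itself change with fewer youths per school.

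**Which share applies.** It differs by outcome. Youths active in 30 days are a subset of those active in 3 months, who are a subset of those ever active. The 30-day ratio therefore has the smallest base. Condom use at last encounter has no time window, so its base is youths who have ever had sex.

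**A separate matter.** D.1 plans "A random sample of 500 rural African American families", divided equally. A 13% loss leaves 500 × 0.87 = 435, about 217 per arm, not 250. The table keeps 250 so that the comparison with the plan is like for like. On 217 per arm, 30–60% active means 65–130 youths, a detectable effect of 0.49–0.35, and power for 0.25 of 30–52%.

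**The case against.** Four points can fairly be made for the plan.

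- **The zero-inflated approach.** The second approach in D.8.2 keeps every youth in the likelihood, and abstainers are scored as zeros. This stands as a description of the model. It does not rescue the power figure, because the condom-use component is still informed essentially by active youths, and D.8.6 gives no figure for it.
- **What D.8.6 names.** It mentions sexual behaviour expressly only for slopes; 0.25 is given for a generic continuous outcome. This stands in part: for a binary outcome such as last encounter the matching figure is the odds ratio of 1.6, which is why both are worked above. But the section claims to cover the models described before it, and those include the sexual-behaviour models.
- **No rate is given.** The remark on abstainers in D.8.1 is general, covers substance use as well, and is not tied to these grades. This stands. Direction and range can be shown; the exact loss cannot.
- **Baseline adjustment.** It might recover some precision. The 0.25 reproduces without any such gain, so the comparison above is on equal terms.

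A reader might also infer stronger things that the documents do not support.

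- **That Aim 2 as a whole is underpowered.** The examples in the aim are unprotected intercourse and multiple partners. The number of unprotected encounters has a value for every youth, so the full sample can apply there.
- **That youths who first have sex during the trial drop out of the baseline-controlled tests.** D.8.2 controls for baseline risk behaviour without requiring a baseline condom value, and D.8.1 specifies full maximum likelihood on all available data. Exclusion would need a complete-case rule the plan does not describe.
- **That the primary outcome should be replaced.** Any all-youth substitute would merge the two kinds of zero that D.8.2 deliberately separates. That is a trade-off for the investigators, not a correction.

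**Conclusion.** The concern holds as a gap in scope. The 0.25 is correct arithmetic for 250 per arm; it does not describe the condom-use comparisons. For the 30-day condom ratio and the condom-use part of the split model, the stated power does not apply.

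The size rests on an assumed active share. At 30–60%, power for an effect of 0.25 is 33–58%, and the detectable odds ratio is about 2.6–1.9. The direction does not depend on that assumption: at 90% active, power is still only about 76% for 0.25 and 73% for 50% against 38%. The figures also assume two-sided tests, negligible school variation, equal active shares in the two arms and, for the odds ratio, a 50% control rate.

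**What to change.** Revise D.8.6 as follows.

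1. State an assumed sexually active share for each condom-use outcome, with its source: activity in the past 30 days for the condom ratio, in the past 3 months for any condom-use analysis on that window, and ever active for last encounter.
2. Give the detectable effect size and odds ratio on the resulting number per arm, over a range of shares such as 30–60%.
3. Limit the 0.25 and 1.6 figures to outcomes that have a value for every youth.
4. Say that the slope and school-adjusted figures also assume the full sample, or recompute them for active youths.

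The cost is a short rewrite and less favourable published figures. It needs no new data and no change to the outcomes or the planned models.
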